### Inclusion Criteria

Patients who meet all of the criteria will be enrolled in the study and the criteria are to (1) have pain that persists or recurs for more than 3 months, (2) receive home-visit rehabilitation, (3) have adequate visual and auditory functions to use the VR equipment, (4) have adequate cognitive and perceptual functions to answer questions measuring subjective symptoms, (5) be at least 20 years of age at the time of consent, and (6) give their free and voluntary written consent to participate in the study, after being fully informed. As the study participants are patients with chronic pain in home care and may have different physical and cognitive ability levels, the following points should be noted; no sensory or cognitive impairment has been diagnosed by the family doctor; the patient is able to see and hear the content with the opportunity to trial the VR before the study begins; and there is a good level of understanding of the research description.

### Exclusion Criteria

Patients who meet any of the criteria will be excluded from the study and the criteria are to (1) have a history of adverse events due to the use of VR devices and (2) are deemed inappropriate for the study by the principal investigator.

### Sample Size

The sample size of 40 cases was not set by statistical detection. It was established based on the median number of cases in reports of studies using immersive VR for pain relief [26-29]. In this study, the targeted number of cases was set based on the assumption that due to the many older patients in the trial, there would be a dropout rate of approximately 15% during the intervention. This dropout rate was based on previous studies that used VR-based rehabilitation interventions [22,30].

### Information on Virtual Reality Devices and Contents

The intervention in this study is VR-applied home-visit rehabilitation. VR will be used during the rehabilitation procedures that the study participants usually engage in.

The VR device used in this study will be Meta Quest 2 (Meta Platforms Inc), which is one of the most widely used VR devices by the general public (Figure 1). Meta Quest is a headset-type VR viewing device, which is worn by fixing on the head a device covering the field of vision. It enables viewing of images in 360 degrees in all directions, in accordance with the frontal orientation of the face, and listening to environmental sounds that accompany the images. The researcher manages the VR device and brings the device to the patient’s home. If the patient has difficulty setting up and fitting the VR device themselves, the researcher will fit or assist them.

**Figure 1 figure1:**
[figure not shown]
The virtual reality device which is used in this study (Meta quest2).

The VR content viewed with Meta Quest 2 will be selected by researchers from natural landscapes available on YouTube VR [31]. This is because one of the VR contents that has the psychological effect of promoting pain relief is landscape [32,33]. In addition, to prevent adverse symptoms associated with the use of VR, the contents that do not change the viewpoint frequently and violently should be selected [34]. In addition, as the participants used VR during their usual rehabilitation, there is no need to perform online operations during VR viewing to avoid affecting the rehabilitation. These will include 10-15 minutes of content of landscapes such as beaches, flower fields, forests, and plateaus (Figure 2). The researcher is present when the VR is used and confirms, and records which content is viewed. The types of landscapes used will be changed regularly so that research participants can experience more than one type of content. The time of the home-visit rehabilitation will be about 40-60 minutes, and VR content will be provided during a part of that time. Rehabilitation will continue while the VR content is being experienced. To ensure the safety of the research participants, VR content will only be provided when they are in a supine or seated position, as wearing the VR equipment will block their full field of vision. Expected adverse events in this study will include pressure sores at the site where the VR equipment is worn, muscle strain from the neck to the shoulders (eg, pain, tightness, and heaviness) due to the load of the VR equipment, and discomfort from viewing VR images (VR sickness) [35], all of which are expected to be mild and tolerable. If any of these adverse events should occur, the VR will be stopped as soon as possible, the patient will be monitored, and medical attention will be sought if necessary.

**Figure 2 figure2:**
[figure not shown]
The virtual reality content is viewed with Meta quest2 (YouTube virtual reality).

### Data Collection

#### Outline

Baseline parameter measurements will be conducted on study participants before the start of the intervention. Baseline measurements will be taken during 3 usual home-visit rehabilitation as (without VR). VR applied home-visit rehabilitation will be carried out once a week, for a total of 10 times. Assessments will be conducted at the baseline, the end of the first intervention, the end of the fifth intervention, and the end of the tenth intervention. Parameter measurements in the study will include pain score, heart rate variability, range of motion, and various patient questionnaires and interviews to evaluate motivation, mood state, catastrophic thoughts of pain, and impressions about VR-applied rehabilitation. For the safety assessment of VR-applied home-visit rehabilitation, the presence and extent of symptoms related to the use of VR equipment and viewing of contents will be ascertained. Data will be collected by the researcher both at baseline and during the VR sessions. The researcher is present and observes the user during the rehabilitation visit, which includes the use of VR and collects and records a range of data. This ensures that the quality of the data collected is controlled. After the end of this clinical study, patients will receive home-visit rehabilitation as usual (without VR; Figure 3).

**Figure 3 figure3:**
[figure not shown]
Outline for data collection. BREQ-2: Behavioral Regulation in Exercise Questionnaire-2; HRV: heart rate variability; PCS: Pain Catastrophizing Scale; POMS 2: Profile of Mood State 2; ROM: range of motion; SF-12: Short-Form Health Survey; VR: virtual reality.

#### Variables

The primary variable is the change in pain from the baseline (before the VR interventions) to the tenth VR intervention. As pain is a subjective symptom of the study participants, it will be subjectively assessed by the Numerical Rating Scale (NRS) on a scale of 0-10, in which 0 indicates no pain at all and 10 indicates the most intense pain experienced so far [36]. The pain as the primary variable will be measured at 3 time points per rehabilitation session: before, during, and after the rehabilitation so that changes between time points will be evaluated.

Secondary variables are heart rate variability (HRV), range of motion (ROM) in the musculoskeletal system area where the pain occurs, motivation for rehabilitation (Behavioral Regulation in Exercise Questionnaire-2 [BREQ-2]), catastrophic thoughts of pain (PCS [Pain Catastrophizing Scale]), mood state (Profile of Mood State 2 [POMS 2]), and quality of life (Short-Form Health Survey [SF-12]).

HRV represents the ability of the heart to respond to physiological and environmental stimuli. Previous studies have shown the feasibility of HRV as a psychophysiological measurement for reactivity to stress [33]. HRV will be measured at the baseline and each VR intervention and changes from the baseline to the tenth intervention will be assessed.

ROM is the range in which each joint of the body can be physiologically exercised without injury or pain. It is one of the outcomes of rehabilitation and is also used to measure the effectiveness in patients with chronic pain [37,38]. ROM of the musculoskeletal system around where the pain occurs will be measured at the baseline and each VR intervention and changes from the baseline to the tenth intervention will be assessed.

The BREQ-2 is a 19-item scale based on self-determination theory to assess behavioral regulation in exercise. BREQ-2 asks questions relating to why they engage in physical activity and exercise, and their responses are measured on a 5-point Likert-type scale ranging from 1 (not true) to 5 (very true). The scale has 5 subscales measuring 5 types of exercise regulations, that are motivation, external regulation, introjected regulation, identified regulation, and intrinsic regulation [39]. The BREQ-2 will be applied at 4 time points, which consist of baseline, first, fifth, and tenth VR interventions and changes in scores between time points will be assessed.

The PCS assesses the extent to which participants experience magnification, rumination, and helplessness in response to their pain episodes [40]. The PCS has 13 items, each scored on a 5-point Likert scale from 0 to 4 (0: not at all, 4: all the time). The PCS is reported as a total composite score (range 0-52), with higher scores indicating greater catastrophic thoughts about pain. PCS scores will be measured at 4-time points, which consist of baseline, first, fifth, and tenth VR interventions, and changes in scores between time points will be assessed.

The POMS 2 questionnaire is used to monitor mood changes, particularly participants’ psychological stress. This scale consists of subjective feelings in 6 different mood states (tension, depression, anger, fatigue, confusion, and vigor). A 5-point Likert scale, ranging from 0 (not at all) to 4 (extremely), is used for each item. The higher scores indicate more pronounced emotions [41]. POMS 2 will be applied at 4-time points, which consist, of baseline, first, fifth, and tenth VR interventions, and changes in scores between time points will be assessed.

A 12-Item SF-12 is a health-related quality of life scale [42]. SF-12 consists of multiple questions to measure eight health concepts, that are physical functioning, limiting physical health problems, bodily pain, general health, vitality, social functioning, limiting emotional problems, and mental health. Information from all 12 items is used to construct physical and mental component summary measures [43]. The SF-12 will be applied at 3 time points, that are baseline, the fifth, and tenth VR interventions, and changes in scores between time points will be assessed.

Through interviews with study participants at the tenth intervention, the effects of VR-applied home-visit rehabilitation will be evaluated, including pain alleviation, promotion of motivation, improvement in mood state and pain catastrophic thinking, and patients’ and families’ impressions.

As part of the safety evaluation, the presence and degree of subjective symptoms will be checked using the NRS, which is expressed on an 11-point scale from 0 to 10, for pressure pain at the site where the VR equipment is worn, muscle strain from the neck to the shoulders due to the load of the VR equipment, and discomfort caused by viewing VR images (VR sickness) [35]. The adverse event NRS will be measured at each VR intervention.

### Safety Evaluation

As part of the safety evaluation, the presence and degree of subjective symptoms will be checked for pressure pain at the site where the VR equipment is worn, muscle strain from the neck to the shoulders due to the load of the VR equipment, and discomfort caused by viewing VR images (VR sickness) [35]. Based on previous studies with patients at home, and also to measure the physical burden of wearing the head-mounted display, these items are measured using the NRS [44]. The adverse event will be measured at each VR intervention.

The condition of study participants will be observed before the start of VR use to check and assess for any problems in using VR; a researcher will be present at all times during the home visit rehabilitation, including the use of VR, to observe any changes in condition. If any participant develops adverse symptoms such as VR sickness at any stage before completing the VR session, the study will be terminated, and the participant will be excluded from the study. The study does not have a follow-up period after the VR sessions for all study participants; however, any patients who have adverse symptoms during the VR sessions will be monitored until their condition has recovered and stabilized.

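### VR symptoms that first appear after a visit are not systematically captured between sessions and have no planned capture after session 10

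*Protocol article*

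**What the plan says.** Timing of the symptom scores. Under Variables, the article states: "The adverse event NRS will be measured at each VR intervention". Safety Evaluation repeats this, and Table 1 ticks VR adverse events at intervention sessions 1 to 10, with no column after session 10. The three items are pressure pain where the headset sits, neck-to-shoulder strain and VR sickness, each rated 0 to 10.

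Expected events. The section on VR devices and contents lists "pressure sores at the site where the VR equipment is worn, muscle strain from the neck to the shoulders", together with VR sickness. It expects all of them to be mild and tolerable.

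Follow-up. Safety Evaluation says: "The study does not have a follow-up period after the VR sessions for all study participants". The same sentence goes on to make an exception: "any patients who have adverse symptoms during the VR sessions will be monitored until their condition has recovered and stabilized".

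Other observation. Safety Evaluation also provides a check before VR use: "The condition of study participants will be observed before the start of VR use to check and assess for any problems in using VR". In addition, "a researcher will be present at all times during the home visit rehabilitation, including the use of VR, to observe any changes in condition".

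Schedule. Under Data Collection, "VR applied home-visit rehabilitation will be carried out once a week, for a total of 10 times". The device section adds: "The time of the home-visit rehabilitation will be about 40-60 minutes, and VR content will be provided during a part of that time". Afterwards, participants return to usual home-visit rehabilitation without VR, and no study data collection is described for that period.

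**The concern.** Two of the three expected harms come from the weight and contact of the headset. Nothing in the article suggests that such effects must show themselves before the visit ends, yet every scheduled score is taken at a visit and the exception to the no-follow-up rule is triggered only by symptoms arising in a session. A strain or pressure injury that is first felt that evening or the next day meets neither condition.

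The study has a single arm and its objective is feasibility, so these scores are the main safety evidence it will produce. The article says that randomized trials will be considered next and that many participants are likely to be older. The limitations it lists are the small number of cases and the lack of blinding and controls. The safety window is not among them, so readers could take in-visit rates as the overall rates of VR-related symptoms.

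**Working it through.** No figure in the article depends on this point, so there is none to reproduce. The check is to trace a symptom through the stated procedures according to when it starts, and then to count the exposures in each category.

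**Tracing by time of onset**

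1. *Starts during a session, any of 1 to 10.* It is scored at that visit, the researcher is present, and the participant is monitored until recovered. This is covered, including after session 10.
2. *Starts after a visit in sessions 1 to 9 and is still present a week later.* The check before VR use, or the score taken at that next visit, may reveal it. The check is not described as scored or as asking about the past week. If the symptom does appear in the next score, nothing stated attributes it to the earlier session. Capture is possible but not systematic.
3. *Starts after a visit in sessions 1 to 9 and resolves before the next.* No stated item asks about the interval, so there is no scored capture.
4. *Starts after session 10.* Table 1 has no later column, no follow-up period exists, and the exception does not apply. There is no planned capture.

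The interview at the tenth intervention does not change this. Its listed topics are pain relief, motivation, mood, catastrophizing, and the impressions of patients and families. Delayed symptoms are not a listed topic, and the interview cannot reach what follows session 10.

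**Counting exposures**

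Inputs: 40 participants and about 15% dropout (Sample Size); 10 weekly sessions (Data Collection). Because the timing of dropout is not given, the counts run from completers only to no dropout.

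- Completers: 40 × (1 − 0.15) = 34.
- All scored participant-sessions: 34 × 10 = 340 to 40 × 10 = 400.
- Sessions 1 to 9, followed by another VR visit about a week later: 34 × 9 = 306 to 40 × 9 = 360.
- Session 10, followed by no planned study contact unless symptoms arose in that session: 34 × 1 = 34 to 40 × 1 = 40.
- Session 10 as a share of exposures among completers: 34/340 = 10%.

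These are counts of exposures, not of missed events. A count of missed events would need the symptom rate per session, the share starting after the visit and the share still present a week later. The article gives none of these.

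**The case against.** The strongest case against the point is that the plan has more safeguards than the no-follow-up clause alone suggests. Much of this stands.

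- A reader who stops at that clause might infer that lingering VR sickness is lost. It is not: the sentence continues with monitoring until recovery for anyone symptomatic in a session, and nothing limits this to sessions 1 to 9.
- A reader might infer that there is no later check at all and that delayed symptoms are missed every week. The check before VR use and the repeat score at the next visit mean that a persisting problem after sessions 1 to 9 could be found.
- A reader might infer that observation ends when the headset is removed. The researcher stays for the whole 40 to 60 minute visit, and the VR content lasts 10 to 15 minutes. That leaves between 40 − 15 = 25 and 60 − 10 = 50 minutes of observed time without VR content, although the article does not say how much of it comes afterwards.
- It is tempting to express the gap as the fraction of the week that is observed, or to assume a share of delayed events. The first measures clock time rather than risk, and the article offers no basis for the second.

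It can also be said that the absence of follow-up is openly stated and contradicts nothing, that events are expected to be mild, and that spontaneous adverse event reporting may be set out in the full protocol. Participants with adverse symptoms in a session are to be excluded, so those who reach session 10 should have had none in the previous nine. These arguments limit the weight of the point. They do not remove it: the schedule and the limit on continued monitoring are stated outright, and spontaneous reporting would not supply scores comparable with those taken at the visits.

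**Conclusion.** The point holds in a limited form. As written, symptoms that first appear after a visit are not systematically captured between sessions 1 and 10 and have no planned capture after session 10. The firm part of its size is that one exposure in ten, 34 to 40 participant-sessions, has no later planned contact for those symptom-free at the visit. For the other 306 to 360, capture depends on an unscored check and on the symptom lasting until the next visit. The number of events missed cannot be calculated.

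The conclusion rests on two assumptions: that some headset-related strain or pressure injury can begin after the visit, which the article neither states nor rules out, and that the full protocol adds no recall question or later contact. This is a gap in safety data that is worth closing because doing so is cheap. It is not an internal contradiction, and the documents do not support saying that the plan is blind to delayed harm.

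**What to change.** Amend Variables, Safety Evaluation and Table 1 as follows.

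- At the start of VR visits 2 to 10, before VR use, record the worst 0 to 10 score since the last session for the same three symptoms.
- If feasible, obtain the same three scores once after session 10, by a brief contact such as a telephone call or at the next usual rehabilitation visit.
- Report the at-session and since-last-session rates separately.
- Where this is not done, state in the report that the symptom rates cover in-visit symptoms only, and list this among the limitations.

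This adds data collection only and leaves the rules on stopping and exclusion as they stand.

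The cost is three questions at visits the researcher already attends, plus one short contact. That contact takes some extra effort, because no researcher attendance is stated for usual visits after the study. The downsides are recall over one week and a possibly higher reported symptom rate. Recruitment began in February 2022 and data collection was still under way in November 2024, so the new scores would exist only for participants still to be treated. The since-last-session rates therefore need their own denominator, and for participants already treated the limitation statement is the only remedy.

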### Ethical Considerations

The study was approved by the Clinical Research Ethics Review Committee of Mie University Hospital (H2021-143) and registered as a clinical trial in “UMIN; University Hospital Medical Information Network” (UMIN000045039). All study participants were informed of the details of the study and gave face-to-face informed consent before the study began. Participants’ data will be anonymized and managed so that personal information cannot be identified.

## Results

Recruitment of participants began on February 22, 2022, and data collection is ongoing as of November 2024. The research results will be published in international peer-reviewed journals and through presentations at national and international conferences.

## Discussion

### Principal Findings

This study will lead to the development of new rehabilitation-based solutions for homebound patients who have difficulty obtaining adequate relief from chronic pain. A rehabilitation program with VR has been reported to alleviate chronic pain [21], and a mechanism of this alleviation is to distract patients from the pain by immersion in VR [19]. However, there is currently insufficient clinical evidence regarding the effects of VR for chronic pain. Especially in home-visit rehabilitation, the feasibility of using VR over the medium to long term and its effectiveness has not been fully clarified.

Existing chronic pain management measures, such as pharmacotherapy, intervention therapy, and psychotherapy, may be difficult to manage adequately because of the risk of side symptoms and the physical and psychosocial burden on the patient [16,17]. Therefore, there is a need for nonpharmacological chronic pain management measures that can be easily implemented at home.

In the current study, exercise-induced pain will be alleviated by using VR during home-visit rehabilitation, thereby increasing ROM. As increased ROM enhances the effectiveness of rehabilitation [45], chronic pain will be improved through rehabilitation. Furthermore, since pain relief with VR alleviates psychophysiological stress conditions [19], HRV should show a state of parasympathetic dominance in the activity of the autonomic nervous system [33]. The improvements in pain will also promote motivation, pain catastrophizing thinking, and mood state, measured by BREQ-2, PCS, and POMS 2, respectively [39-41], even in homebound patients who are difficult to motivate and have poor psychosocial health [9,10]. The experience of (simulated) natural landscapes brought about by VR will improve psychosocial factors in homebound patients, who infrequently leave their homes, and help improve quality of life in the medium to long term measured by SF-12 [42,43].

Therefore, this study will contribute to the development of novel rehabilitation-based solutions for homebound patients who have had difficulty obtaining adequate relief from chronic pain.

Although VR is generally considered to be a safe and noninvasive procedure with few side effects, the use of VR has been reported to induce VR sickness [35]. One must be aware of the potential occurrence of VR sickness and carefully observe the patient’s condition during the administration of VR. It is assumed that many patients at home are older adults, which may be a barrier to the introduction of VR into home rehabilitation. For VR to be successfully applied to older people, careful induction sessions are important, and the process needs to be evaluated. Limitations of this feasibility study are the small number of cases as well as the lack of blinding and controls.

